## Abstract

**Background:**

High rates of anxiety, depression and unmet needs are evident amongst haematological cancer patients undergoing treatment and their Support Persons. Psychosocial distress may be minimised by ensuring that patients are sufficiently involved in decision making, provided with tailored information and adequate preparation for potentially threatening procedures. To date, there are no published studies evaluating interventions designed to reduce psychosocial distress and unmet needs specifically in patients with haematological cancers and their Support Persons. This study will examine whether access to a web-based information tool and nurse-delivered telephone support reduces depression, anxiety and unmet information needs for haematological cancer patients and their Support Persons.

**Methods/Design:**

A non-blinded, parallel-group, multi-centre randomised controlled trial will be conducted to compare the effectiveness of a web-based information tool and nurse-delivered telephone support with usual care. Participants will be recruited from the haematology inpatient wards of five hospitals in New South Wales, Australia. Patients diagnosed with acute myeloid leukaemia, acute lymphoblastic leukaemia, Burkitt’s lymphoma, Lymphoblastic lymphoma (B or T cell), or Diffuse Large B-Cell lymphoma and their Support Persons will be eligible to participate. Patients and their Support Persons will be randomised as dyads. Participants allocated to the intervention will receive access to a tailored web-based tool that provides accurate, up-to-date and personalised information about: cancer and its causes; treatment options including treatment procedures information; complementary and alternative medicine; and available support. Patients and Support Persons will complete self-report measures of anxiety, depression and unmet needs at 2, 4, 8 and 12 weeks post-recruitment. Patient and Support Person outcomes will be assessed independently.

**Discussion:**

This study will assess whether providing information and support using web-based and telephone support address the major psychosocial challenges faced by haematological patients and their Support Persons. The approach, if found to be effective, has potential to improve psychosocial outcomes for haematological and other cancer patients, reduce the complexity and burden of meeting patients’ psychosocial needs for health care providers with high potential for translation into clinical practice.

**Trial registration:**

ACTRN12612000720819.

## Background

### Burden of haematological cancers

Haematological malignancies include leukaemias, lymphomas and myelomas. Together, haematological malignancies represent 9% of all cancers in the economically developed regions of the world, and are the fourth most common type of cancer [1]. Five year relative survival rates for haematological malignancies vary depending on a range of factors including the type of cancer and patient age. In Australia, 5-year relative survival rates range from 24% for acute myeloid leukaemia [2] to 87% for Hodgkin lymphoma [2].

### Psychosocial wellbeing of individuals with haematological cancers

Treatments for haematological cancers can include intensive chemotherapy, radiotherapy, surgery and haematopoietic stem cell transplantation [3-6]. Treatments are often urgent and result in debilitating side effects including nausea, depression, fatigue, vomiting, diarrhoea, oral mucositis, ovarian failure and infertility [7-9]. Unlike many other types of cancers, treatment for haematological malignancies often requires long periods of hospitalisation and isolation to prevent infections [10,11]. Given the aggressive and complex treatments required, it is not surprising that levels of cancer-related distress are high. Rates of anxiety amongst haematological cancer patients range from 22% [12] to 27% [13], and rates of depression between 17% [12] and 31% [13]. Unmet needs remain high even after active treatment has ceased, with 27% of haematological cancer survivors reporting unmet needs related to finances, emotional support, and information [14].

### Significant burden placed on support persons

Support Persons are individuals identified by patients as a main source of support in coping with cancer and its treatment. They might be the patient’s spouse, child, other family member, or friend. Support Persons play an essential role in providing emotional and practical support to patients [15], however many report that they have inadequate education and skills to undertake this role [16]. The significant burden placed on Support Persons often results in psychological morbidity, including anxiety and depression, as well as adverse effects on physical health, work and family commitments, and finances [17-19]. Caregivers of haematological cancer patients report needing information about managing side effects and symptoms, and giving medications [16]. Among the most important factors identified by Support Persons of haematological cancer patients for improving their own quality of life are improved communication with health care providers and receiving education and support [16].

### Evidence-based strategies for reducing psychosocial distress

A substantial amount of research has examined strategies to reduce psychosocial distress among individuals with cancer. Although little work has been done with patients diagnosed with haematological cancers, the substantial amount of research with other cancer patient groups suggests psychosocial distress can be minimised by:

#### Ensuring that patients are involved in decision making

Decisional support for treatment has been linked to a number of positive outcomes including greater knowledge, more realistic expectations and a better match between patient values and decisions [20]. There is considerable variation, however, in patient preferences for the extent of involvement in decision making regarding their cancer care [21]. Therefore the ability of clinicians to accurately identify patient preferences for involvement in treatment decisions is critical. Research has shown that in 58% of cases clinicians do not accurately assess patient preferences [21,22]. Effective forms of communication that account for individual factors, such as health literacy and patient preference, are essential to provide patients with an opportunity to take an active role in decision making about their health care.

#### Providing tailored information

The principle of patient-centeredness endorsed by the Institute of Medicine promotes health care that is tailored and responsive to patient needs [23]. Providing patients with information about treatment, including both procedural and sensory information, can reduce patient distress and improve recovery [24-26]. Despite these potential benefits, many cancer patients report high levels of unmet information needs [27]. Guidelines for the psychosocial care of cancer patients recommend that information is tailored to individual circumstances and preferences for amount and type of information [28]. Tailoring is likely to be particularly important for haematological cancer patients and their Support Persons given that haematological cancers are a very diverse group of diseases that often require a range of complex and rapidly changing treatment regimes. Customising diagnosis and treatment information to ensure concordance with the medical circumstances of the individual may help to prevent unnecessary anxiety as a result of viewing information that is not relevant [28]. Providing an opportunity for patients and their families to talk to an experienced cancer nurse can improve understanding and reduce psychosocial morbidity [28]. Patients vary in their preferences for the amount of information they wish to receive, the way the information should be presented and the level of detail they would like to know [29]. Tailoring information to match individual preferences and health literacy can improve psychosocial outcomes and recall of information [23,28,30].

#### Preparing patients for potentially threatening procedures

High levels of anxiety can result in poor recall of information, which has implications for patient adherence to recommendations for care [31]. The prevalence of pre-treatment anxiety is very high among patients undergoing cancer treatment [32]. While there is evidence that preparing patients for potentially threatening medical procedures can reduce anxiety and pain, and improve recovery, information provision prior to treatment is often inadequate [28]. Therefore, there is potential to improve psychosocial outcomes for cancer patients via integration of preparatory information into routine care.

#### Providing psychological therapies

There is substantial evidence for the effectiveness of psychological therapies, including supportive and cognitive-behavioural therapies, for reducing treatment-related distress in cancer patients [28]. Meta-analyses have demonstrated the effectiveness of psychological therapies, finding significant improvements across a range of outcomes for cancer patients including: emotional adjustment, social functioning, quality of life, anxiety, depression, and physical symptoms. [33,34] While there is demonstrated success in improving outcomes for patients who access psychological therapies, the high prevalence of anxiety^12 13^, depression^12 13^ and unmet needs [14] among individuals with cancer suggest there may be barriers to accessing such treatments. Barriers to the use of psychological support services reported by patients include a lack of patient awareness of services, lack of provider referral/endorsement, inconvenient location of services, lack of willingness to talk to a stranger or therapist about personal issues, and difficulty scheduling appointments around treatment and other commitments [35,36].

### The Internet is an ideal platform to provide support which aligns with the evidence base

Most Australians have access to the Internet (83%) [37], and it is frequently reported as an important source for obtaining medical information [38]. There are a number of advantages in using web-based interventions for information provision and psychosocial support: information can be tailored based on user circumstances (e.g. diagnosis), needs and preferences using algorithms; users can exercise control over the type and level of information they receive and the frequency with which they access the information; it allows for real-time customisation based on user needs and preferences (e.g. text size); information can be presented in a range of formats including text, graphics and videos to suit the literacy levels of users, thereby improving understanding and recall; and web-based interventions can incorporate interactive features to facilitate communication and information sharing, such as email and discussion forums. From a service provider perspective, a major advantage of web-delivered interventions is that it enables central delivery of standardised evidence-based information independent of resource constraints of individual health care settings [39]. A web-based approach can also be used to facilitate access to information and support for Support Persons.

### Web-based interventions to improve psychosocial outcomes for patients and their Support Persons

Several reviews have investigated the effectiveness of web-based approaches for patient education and psychosocial support. [40-43] These reviews have demonstrated some evidence in favour of web-based interventions for improving patient outcomes, including knowledge, healthy behaviours, social support and psychosocial wellbeing. However, the conclusions drawn from the literature are limited by mixed findings and methodological weaknesses of the available studies. Furthermore, given that there are no published studies evaluating web-based interventions designed to improve psychosocial outcomes specifically for patients with haematological cancers and their Support Persons, there is a need to further develop this evidence base. The potential for web-based interventions to improve psychosocial outcomes for haematological cancer patients is likely to be enhanced by ensuring that interventions are integrated, tailored to the needs and preferences of the patient, involve Support Persons, provide support for treatment decision making and preparation for treatment, and provide support across the pre-treatment, treatment and post-treatment phases of illness.

### Aims

This study will examine, using a randomised controlled trial, whether an integrated approach that includes access to a web-based information tool and nurse-delivered telephone support reduces for both haematological cancer patients and their Support Persons (i) unmet information needs (primary outcome); and (ii) depression; and (iii) anxiety (secondary outcomes); at 2, 4, 8 and 12 weeks follow up.

### Hypotheses

It is hypothesised that:(i)Patients who are allocated to the intervention group will have a 0.45 standard deviation lower mean total score on the Health System and Information Needs Domain of the Supportive Care Needs Survey Short Form (SCNS-SF34) (primary outcome), and 0.45 standard deviation lower anxiety and depression scores as measured by the Hospital Anxiety and Depression Scale (HADS) (secondary outcomes), compared to patients who are allocated to the control condition;(ii)Support Persons who are allocated to the intervention group will have a 0.45 standard deviation lower unmet information needs score as measured by the Support Persons Unmet Needs Survey (SPUNS) (primary outcome), and a 0.45 standard deviation lower depression and anxiety score as measured by the Depression and Stress Scale-21 (DASS) (secondary outcomes), compared to Support Persons who are allocated to the control condition.

## Method

### Study design

This study is a non-blinded, parallel-group, multi-centre randomised controlled trial comparing the effectiveness of a web-based information tool and nurse-delivered telephone support with usual care. The primary outcomes for both patients and Support Persons are unmet information needs and the secondary outcomes are anxiety and depression. All outcomes are assessed a 2, 4, 8 and 12 weeks post-recruitment. This study is funded by a Cancer Institute New South Wales Translation Program Grant (10/THS/2-14).

### Hospital eligibility

Participants will be recruited from the haematology inpatient wards of five Australian hospitals located in New South Wales. These hospitals were selected because they treated at least 15 eligible participants each year.

### Patient and support person eligibility

Patients will be eligible to participate if they are: aged 18 years or older; English speaking; newly diagnosed with acute myeloid leukaemia, acute lymphoblastic leukaemia, Burkitt’s lymphoma, Lymphoblastic lymphoma (B or T cell), or Diffuse Large B-Cell lymphoma; are potentially making a decision regarding treatment; have a life expectancy of 2 months or more as judged by their clinician; and are able to provide informed consent. Those who have commenced cytotoxic chemotherapy will be excluded. The included haematological malignancies were chosen to represent aggressive malignancies that frequently require urgent inpatient treatment. Support Persons of patients are eligible to participate if they are: aged 18 years or older; able to provide informed consent; and are nominated by the patient participant to be an important source of support in relation to the demands of their cancer diagnosis and treatment. Patients and Support Persons are not required to have access to the internet as the intervention will be available to access using iPads provided in hospital.

### Recruitment and consent procedure

A consecutive sample of haematological cancer patients and their Support Persons will be recruited. Recruitment will take place as soon after the time of diagnosis as possible. Patients will be informed about the research by their treating doctor and provided with a study information statement. Participants who are willing to take part will complete a consent form which will be co-signed by their doctor. Consenting patients will be provided with an information package to pass on to their Support Person if they wish to do so. The information package contains a study information statement for the Support Person detailing the research and what participation would involve. Support Persons who are willing to take part in the study will be instructed to complete an enclosed consent form and return it to the research team using the reply paid envelope provided. Patients are eligible regardless of whether they have a participating Support Person. Support Persons are only eligible to participate if they are supporting a cancer patient who has also consented to participate. In the event of the death or withdrawal of a patient participant, the consenting Support Person, if any, will be asked whether they would like to continue participation.

### Randomisation and blinding

Patients will be allocated to either the intervention or control group depending on the week they are recruited, with weeks randomly allocated to intervention or control group across all hospitals throughout the recruitment period. Support Persons will be allocated to the same group as the patient. The random allocation sequence will be generated using an online random number generator distributed by a research team member not involved in participant recruitment. Participants and health care providers will be blind to the allocation sequence. Clinical trials nurses managing the study at each hospital will be informed by the researchers at the start of each week whether participants recruited over the next week are to be assigned to the intervention or control conditions. Due to the nature of the intervention, it is not possible to blind participants or health care providers to condition allocation. Those responsible for conducting analysis of outcomes and interpretation of data will be blind to group allocation.

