### Sample size

Patient sample: Assuming a 75% consent rate, 450 patients will be approached to give a sample of 340 at baseline. Allowing for 15% attrition, at each follow up, a sample of 145 per group will be available at 4 weeks, 123 per group at 8 weeks and 105 per group at 12 weeks. Assuming 90% power and 5% significance level this will enable detection of differences between groups of, 0.38 standard deviations (SD) at 4 weeks, 0.41 SD at 8 weeks and 0.45 SD at 12 weeks follow up. There are over 400 patients diagnosed each year in NSW with the cancers specified in our eligibility criteria. High volume centres will be targeted for recruitment. Current studies being conducted by the group involving clinic-based recruitment are achieving an 85% consent rate. These effect sizes are clinically relevant.

Support person sample: For each of the 340 patient participants, one Support Person will be recruited. It is anticipated that 80% of patients will have a Support Person who provides data at 4 weeks. Allowing for 15% attrition at each follow up, a sample of 115 per group will be available for comparison at 4 weeks, 100 per group at 8 weeks and 85 per group at 12 weeks. Assuming 90% power and 5% significance level this will enable detection of differences between groups of 0.4 SD at 4 week follow up and 0.45 SD at 8 weeks and 0.5 SD follow up. These effect sizes are clinically relevant.

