### Statistical analysis

The primary outcome of interest will be scores on the Health Systems and Information Needs Domain of the SCNS-34 (patients), and the information and relationships domain of the SPUNS (Support Persons). Secondary outcomes will be scores on the anxiety and depression subscales of the HADS (patients) and DASS (Support Persons). Outcomes will be compared between groups at each time point using a mixed effects linear regression that includes data from all time points (including baseline), with fixed effects for group, time, the interaction between time and group, and clinic. The model will be adjusted for age and gender (of participant or Support Person as appropriate) and robust variance estimates will be obtained. Treatment group comparisons at each visit will be estimated by differences in least-square means from the group by visit interaction and will be presented as differences in means with 95% Confidence Intervals and accompanying p values. Primary analysis will involve complete case analysis, and sensitivity analysis will be performed using multiple imputation to account for missing data. If the distribution is problematic, we will consider alternative strategies such as a transformation.

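### Recruitment weeks are the unit of randomisation, but the sample size allows for no between-week clustering and the analysis does not say how week is handled

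*Protocol article*

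**What the plan says.** Under Randomisation and blinding, a patient's arm depends on the week of recruitment, "with weeks randomly allocated to intervention or control group across all hospitals throughout the recruitment period". Trial nurses learn at the start of each week which arm applies to that week's recruits. Partners in a pair stay together: "Support Persons will be allocated to the same group as the patient". The abstract describes the scheme only as "Patients and their Support Persons will be randomised as dyads" and does not mention the week.

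Under Sample size, the patient figures start from "Assuming a 75% consent rate, 450 patients will be approached to give a sample of 340 at baseline". After 15% attrition at each follow-up, "a sample of 145 per group will be available at 4 weeks, 123 per group at 8 weeks and 105 per group at 12 weeks". The resulting claim is "Assuming 90% power and 5% significance level this will enable detection of differences between groups of, 0.38 standard deviations (SD) at 4 weeks", then "0.41 SD at 8 weeks and 0.45 SD at 12 weeks follow up". No number of weeks, cluster size, ICC or design effect is given.

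Under Statistical analysis, the outcome model is a mixed effects linear regression "with fixed effects for group, time, the interaction between time and group, and clinic", adjusted for age and gender. Robust variance estimates are promised, but the level at which they are clustered is not stated, and no random effects are named.

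**The concern.** When whole weeks are randomised, two patients recruited in the same week cannot end up in different arms. Anything that makes same-week recruits alike, such as season or who is put forward in a week whose arm is already known to staff, therefore adds variance to the treatment contrast itself. A calculation that treats patients as independently allocated leaves this variance out.

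Two things are at stake. The first is whether the trial has the power it states for its primary outcome. The second is whether the confidence intervals and p values reflect the allocation actually used. The clinic fixed effect does not help, because each week's allocation cuts across all five hospitals. Clinic absorbs stable hospital differences, not differences between weeks.

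**Working it through.** **Inputs from the article.** 340 patients, 15% attrition per follow-up, 145, 123 and 105 per group, 90% power and 5% significance (Sample size); five hospitals with at least 15 eligible patients a year each (Hospital eligibility); 75% consent (Sample size).

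**Assumed, because the article does not give them.** Between-week ICC of 0.01 to 0.10; recruitment of 340 patients over six to two years (312 to 104 weeks); Poisson weekly counts; a two-sided test.

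**1. Reproduce the stated figures.** 340/2 = 170 per group. 170 × 0.85 = 144.5; 170 × 0.85² = 122.8; 170 × 0.85³ = 104.4. These match 145, 123 and 105.

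For individual randomisation the detectable difference is (1.960 + 1.282) × √(2/n):
- n = 145: 0.381 SD (stated 0.38)
- n = 123: 0.413 SD (stated 0.41)
- n = 105: 0.447 SD (stated 0.45)

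Power at the stated differences is 89.9%, 89.5% and 90.3%. A one-sided test would give 0.344, 0.373 and 0.404, which does not match. The patient figures therefore imply a design effect of 1.

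**2. Design effect for weekly clusters.** With cluster sizes m, DE = 1 + (Σm²/Σm − 1) × ICC. For Poisson counts with mean λ analysed patients per week, Σm²/Σm = λ + 1, so DE = 1 + λ × ICC.

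- 12 weeks, 210 analysed: λ = 210/312 = 0.67 to 210/104 = 2.02
- 4 weeks, 290 analysed: λ = 290/312 = 0.93 to 290/104 = 2.79

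**3. Consequences.** Effective n per group is n/DE. Power is Φ(d√(n/(2·DE)) − 1.960). Type I error if week is ignored is 2(1 − Φ(1.960/√DE)).

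Worked case (12 weeks, two years, ICC 0.10): DE = 1 + 2.02 × 0.10 = 1.20; effective n = 105/1.202 = 87.4; detectable difference = 3.24 × √(2/87.4) = 0.49 SD; power for 0.45 SD = Φ(2.975 − 1.960) = 84.5% (84.1% using the t distribution); type I error = 2(1 − Φ(1.788)) = 7.4%.

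| Follow-up | Recruitment | ICC | DE | Detectable SD | Power at stated SD | Type I error, week ignored |
|---|---|---|---|---|---|---|
| 12 wk | 6 years | 0.01 | 1.01 | 0.45 | 90.1% | 5.1% |
| 12 wk | 6 years | 0.05 | 1.03 | 0.45 | 89.4% | 5.4% |
| 12 wk | 6 years | 0.10 | 1.07 | 0.46 | 88.4% | 5.8% |
| 12 wk | 2 years | 0.01 | 1.02 | 0.45 | 89.8% | 5.2% |
| 12 wk | 2 years | 0.05 | 1.10 | 0.47 | 87.4% | 6.2% |
| 12 wk | 2 years | 0.10 | 1.20 | 0.49 | 84.5% | 7.4% |
| 4 wk | 6 years | 0.01 | 1.01 | 0.38 | 89.6% | 5.1% |
| 4 wk | 6 years | 0.05 | 1.05 | 0.39 | 88.6% | 5.5% |
| 4 wk | 6 years | 0.10 | 1.09 | 0.40 | 87.2% | 6.1% |
| 4 wk | 2 years | 0.01 | 1.03 | 0.39 | 89.1% | 5.3% |
| 4 wk | 2 years | 0.05 | 1.14 | 0.41 | 85.8% | 6.6% |
| 4 wk | 2 years | 0.10 | 1.28 | 0.43 | 81.6% | 8.3% |

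**4. Where the article places the pace.** Its floor is 5 × 15 × 0.75 = 56 consenting patients a year, about 1.1 a week, or 340/56 ≈ 6 years. The six-year rows are therefore the floor. At ICC 0.05 they lose 90.3 − 89.4 = 0.9 points of power at 12 weeks and 89.9 − 88.6 = 1.3 points at 4 weeks.

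**The case against.** The strongest reply is that the article does not show that the analysis ignores week. It lists only the fixed effects of a mixed model and names no random effects, not even one for the person, so the random part may simply have been condensed out. If the promised robust variance is clustered on week, the intervals are sound. This stands. A reader might infer that the standard errors are certainly too small, or that the robust variance will by default be clustered on the person. The article supports neither. It leaves the level open.

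Second, the size depends on an ICC found nowhere in the article, and with an ICC near zero nothing changes. Weekly clusters are also small at the floor pace. Both points stand, so the results are given as a range. One-year recruitment would give worse figures, but it would mean approaching 450 patients in a year when the article counts just over 400 diagnoses a year in the whole state.

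Third, the discussion forum and the study nurse might look like sources of week-level similarity. They are shared across the whole intervention arm, whatever the recruitment week, so they do not support this point.

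Fourth, the abstract's wording on dyads may look like a flat contradiction. It is weaker than that: pairs are allocated together, and the abstract leaves out the week.

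What the reply does not answer is the sample size. Its patient figures are given in full and contain no allowance for the unit randomised.

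**Conclusion.** The point holds in conditional form. The week is the unit of randomisation, the patient sample size uses a design effect of 1, and the analysis text neither lists a week term nor ties the robust variance to week. For any positive between-week ICC the stated 90% power is somewhat overstated. Confidence intervals will be too narrow if week is left out of the analysis.

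Under the assumed ICC of 0.01 to 0.10 and six to two years of recruitment, the 12-week design effect is about 1.01 to 1.20. Power for 0.45 SD falls from about 90% to about 84%, the detectable difference is 0.45 to 0.49 SD, and type I error with week ignored is 5.1% to 7.4%. The worst corner at 4 weeks is about 82% power and 8.3% type I error. At the floor pace, with ICC up to 0.05, the loss is under 2 points. A large loss is therefore possible but not shown.

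These sizes are for patients. Support Persons inherit the weekly allocation, so the direction is the same. Their stated 4-week figure, however, does not reproduce even without clustering (115 per group detects 0.43 SD, not 0.4), which is a separate matter.

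Severity: should be fixed. The reason is the mismatch between allocation and calculation, not a demonstrated large loss.

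**What to change.** - **Analysis:** include a random intercept for recruitment week, or state that the robust variance is clustered on recruitment week. Base the degrees of freedom on the number of weeks.
- **Sample size:** state the expected number of recruitment weeks and a range for the between-week ICC, and restate the detectable differences using DE = 1 + λ × ICC.
- **Abstract:** say that dyads are allocated together by recruitment week.

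The cost is small. Recruitment week is already known for every participant, the allocation scheme is unchanged and no extra patients are needed. The stated detectable differences become slightly less favourable. Switching to randomisation of individual dyads would be a redesign and is not needed to resolve this point.

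### One weekly allocation appears to be shared by all five hospitals, so effects common to a week fall wholly on one arm; separate sequences per hospital would be a cheap, modest gain

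*Protocol article*

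**What the plan says.** Under Randomisation and blinding, the arm depends on the week of recruitment, "with weeks randomly allocated to intervention or control group across all hospitals throughout the recruitment period". The sequence is described in the singular: "The random allocation sequence will be generated using an online random number generator". The trials nurses at each hospital are "informed by the researchers at the start of each week whether participants recruited over the next week are to be assigned" to intervention or control. Support Persons follow the patient's allocation.

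Under Hospital eligibility there are five sites: "Participants will be recruited from the haematology inpatient wards of five Australian hospitals located in New South Wales". On volume, the article says only: "These hospitals were selected because they treated at least 15 eligible participants each year".

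The mixed model under Statistical analysis is specified "with fixed effects for group, time, the interaction between time and group, and clinic", adjusted for age and gender. It has no term for week of recruitment. No recruitment period is stated.

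**The concern.** If one arm is drawn per calendar week and used everywhere, arm is a fixed function of week. Within a week there is no concurrent comparison at another site to offset what is peculiar to that week, such as a holiday period affecting all wards. Adjusting for clinic does not help, because a week effect of this kind cuts across clinics. Week entered as a fixed effect would be completely aliased with treatment.

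With a separate sequence at each hospital, weeks in which two or more hospitals recruit would often contain both arms, and shared week effects would partly cancel. Better modelling alone cannot supply that, so the point is distinct from whether weeks are allowed for in the analysis or sample size. At stake are some precision against the planned 90% power and the balance of arm sizes against the planned equal groups.

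**Working it through.** **Inputs from the article.** Five hospitals, each with at least 15 eligible patients a year. On recruitment: "Assuming a 75% consent rate, 450 patients will be approached to give a sample of 340 at baseline". On retention: "a sample of 145 per group will be available at 4 weeks, 123 per group at 8 weeks and 105 per group at 12 weeks". Power is 90% at the 5% level, for 0.45 SD at 12 weeks.

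**Assumptions, because the article gives no figure.** Recruitment lasts W = 52, 104, 156, 208 or 312 weeks. The last follows from the volume floor: 5 × 15 = 75 a year, 450 / 75 = 6 years, 6 × 52 = 312 weeks. Patients arrive at random (Poisson), evenly over hospitals, and weeks are randomised 1:1 without blocking. A share rw of outcome variance is common to patients recruited in the same week at any hospital.

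**1. The plan's own figure.** Detectable difference = (1.960 + 1.282) × √(2/105) = 0.447 SD, against the stated 0.45. Power for 0.45 SD with 105 per group is 0.903. The figure reproduces, on the basis of individual randomisation.

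**2. Randomised units.** Nominally W weeks against 5W hospital-weeks. Units that contain at least one of the 340 patients:
- shared: W(1 − exp(−340/W))
- per hospital: 5W(1 − exp(−68/W))

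For W = 104: 104 × (1 − exp(−3.27)) = 100, and 520 × (1 − exp(−0.654)) = 250. So about 270 of the 520 hospital-weeks would be empty.

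**3. Power at 12 weeks (210 patients, 0.45 SD).** Let λ = 210/W. Under the shared sequence the design effect is about 1 + λ·rw. Under separate sequences, patients recruited in the same week at different hospitals are as likely to be in opposite arms as in the same arm, so their covariance cancels on average and the design effect is about 1 + (λ/5)·rw. Power uses 105 divided by the design effect as the size per group.

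For W = 104 and rw = 0.05, λ = 2.02. The design effects are 1.101 and 1.020, and the powers 0.874 and 0.898.

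| W | Occupied weeks | Occupied hospital-weeks | Fewer units if shared | Power, rw = 0.02: shared / separate | Power, rw = 0.05: shared / separate |
|---|---|---|---|---|---|
| 52 | 52 | 190 | 73% | 0.880 / 0.899 | 0.845 / 0.892 |
| 104 | 100 | 250 | 60% | 0.892 / 0.901 | 0.874 / 0.898 |
| 156 | 138 | 276 | 50% | 0.896 / 0.902 | 0.884 / 0.900 |
| 208 | 167 | 290 | 42% | 0.898 / 0.902 | 0.889 / 0.900 |
| 312 | 207 | 305 | 32% | 0.900 / 0.903 | 0.894 / 0.901 |

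A simulation that also adjusts for clinic (W = 104, 3,000 recruitment and allocation draws per scenario) gives 88.2% against 89.1% at rw = 0.02, and 86.4% against 88.8% at rw = 0.05. Those gaps of 0.9 and 2.4 points agree with the table. If rw = 0 there is no gap. If the correlation arises only among patients of the same hospital and week, both schemes have the same design effect and again there is no gap.

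**4. Arm sizes.** With simple randomisation of units, the variance of one arm's size is (N/4)(1 + m), where m is the mean number of patients per unit. For N = 340 and W = 104:
- shared, m = 3.27: SD = √(85 × 4.27) = 19.1; 95% range 170 ± 37, about 133 to 207
- separate, m = 0.65: SD = √(85 × 1.65) = 11.9; 95% range 170 ± 23, about 147 to 193

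This does not add an average loss of precision in the clinic-adjusted model. In the simulation, the variance relative to 4/N at rw = 0.02 is 1.075 (shared) and 1.043 (separate). Taking off the week parts, 2.02 × 0.02 = 0.040 and 0.40 × 0.02 = 0.008, leaves 1.035 for both. Within any one hospital the number of randomised weeks is W under either scheme.

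**The case against.** - **Wording.** The phrase about hospitals could mean only that the scheme runs at every site. Hospital-specific sequences are not strictly excluded, and a journal article is condensed. That stands as a caution, but nothing in the article describes separate lists, and the sequence is singular.
- **Preference, not error.** A reader might infer that tying arm to calendar week biases the comparison. The document does not support that: weeks are randomised, so week effects enter as chance imbalance over many weeks. Nothing in the article is contradicted either. This stands.
- **Four-fifths of the randomisation wasted.** A reader might infer this from W against 5W. It is a nominal count that includes empty hospital-weeks, and a lower count costs precision only through variance shared across hospitals. This stands.
- **The shared variance may be very small.** Staff changes are usually local to one hospital. Changes in usual care outlast a week and so reach both arms. Outcomes are measured 2 to 12 weeks after recruitment, so patients from neighbouring weeks live through much the same period. The document gives no value for rw. This stands, and is why a range that includes zero is shown.
- **Short recruitment periods flatter the point.** Approaching 450 patients in 104 weeks means 225 a year, against the article's figure of just over 400 diagnosed yearly in NSW; 52 weeks would need 450 in one year. At the volume floor the gap is below 1 point. This also stands.
- **Blocking of weeks could narrow the arm-size range without five sequences.** True; the article does not say whether weeks are balanced.

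None of this gives a reason to prefer a shared sequence. On precision, separate sequences are never worse.

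**Conclusion.** The point holds as a cheap improvement to the design, not as an error. As most naturally read, the scheme puts all hospitals in the same arm each week, so an effect shared across hospitals in a week cannot be offset within that week.

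The size is modest and conditional. The cost at 12 weeks is about 1 point of power if rw = 0.02 and 2.4 points if rw = 0.05 over 104 weeks, 0.7 points at rw = 0.05 over 312 weeks, and nil if rw = 0 or the correlation is only within a hospital. The wider spread of arm sizes is a matter of balance and assumes unblocked weeks. Recruitment period and rw are assumptions throughout.

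**What to change.** In Randomisation and blinding, replace the single sequence with five independent random sequences of weeks, one per hospital, generated by the same team member. Tell each hospital's nurse only that hospital's arm for the week, and state that the randomised unit is the hospital-week. If separate sequences were already intended, say so. If a shared one was chosen on purpose, give the reason.

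The cost is five lists instead of one, a separate weekly message to each hospital, and a small risk of a wrong-arm message. No extra patients, staff or visits are needed. Contamination does not worsen, because each ward already alternates between arms.

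The change leaves two matters untouched that need their own answer: recruiting staff still know the arm before they recruit, and neither the sample size nor the model allows for week of recruitment.
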